## Abstract

**Background:**

Ischemic heart disease (IHD) is the most common cause of heart failure (HF); however, the role of revascularization in these patients is still unclear. Consensus on proper use of cardiac imaging to help determine which candidates should be considered for revascularization has been hindered by the absence of clinical studies that objectively and prospectively compare the prognostic information of each test obtained using both standard and advanced imaging.

**Methods/Design:**

This paper describes the design and methods to be used in the Alternative Imaging Modalities in Ischemic Heart Failure (AIMI-HF) multi-center trial. The primary objective is to compare the effect of HF imaging strategies on the composite clinical endpoint of cardiac death, myocardial infarction (MI), cardiac arrest and re-hospitalization for cardiac causes.

In AIMI-HF, patients with HF of ischemic etiology (n = 1,261) will follow HF imaging strategy algorithms according to the question(s) asked by the physicians (for example, Is there ischemia and/or viability?), in agreement with local practices. Patients will be randomized to either standard (SPECT, Single photon emission computed tomography) imaging modalities for ischemia and/or viability or advanced imaging modalities: cardiac magnetic resonance imaging (CMR) or positron emission tomography (PET). In addition, eligible and consenting patients who could not be randomized, but were allocated to standard or advanced imaging based on clinical decisions, will be included in a registry.

**Discussion:**

AIMI-HF will be the largest randomized trial evaluating the role of standard and advanced imaging modalities in the management of ischemic cardiomyopathy and heart failure. This trial will complement the results of the Surgical Treatment for Ischemic Heart Failure (STICH) viability substudy and the PET and Recovery Following Revascularization (PARR-2) trial. The results will provide policy makers with data to support (or not) further investment in and wider dissemination of alternative ‘advanced’ imaging technologies.

**Trial registration:**

NCT01288560

## Background

The multifaceted Canada-Finland collaborative research program, Imaging Modalities to Assist with Guiding Therapy and the Evaluation of Patients with Heart Failure (IMAGE-HF), is designed with the following overall objectives: 1) to determine the impact of emerging imaging strategies on relevant clinical outcomes and decision making in patients with HF; 2) to establish standardized quality assurance (QA) measures and central databases in order to achieve reliable outcome driven research; and 3) to apply this as a platform for evaluation of new and emerging imaging and serum biomarkers in HF. The program consists of three separate randomized controlled trials. Project 1A is designed to compare the effect of HF imaging strategies in the evaluation and diagnosis of ischemic heart disease (IHD). Project 1B evaluates the utility of cardiac magnetic resonance (CMR) imaging in addition to standard echocardiography in the evaluation and diagnosis of non-ischemic HF (with either preserved or reduced ejection fraction) in comparison to the standard echocardiography alone. Project 1C is comparing two imaging modalities for the detection of coronary artery disease (standard coronary angiography versus cardiac computerized tomography scans).

### Project 1A is the focus of this publication

Despite multiple advances in cardiovascular disease, the morbidity and mortality of patients with heart failure (HF) in the setting of IHD remains high. Although it is believed that most patients with symptoms of significant ischemia may benefit from revascularization, decisions regarding revascularization in those with advanced ventricular dysfunction and no significant ischemia are complex, and the applicability of current clinical trial data is often challenged by limited patient selection. Over the past three decades, information describing cardiac structure, function, perfusion, hemodynamics, and metabolism obtained from noninvasive cardiac imaging studies has been used to guide management decisions for patients with HF. Although this anatomic and physiologic information adds value to clinical care, an accepted strategy is still debated regarding the optimal testing sequence approach to efficiently identify the treatment strategy most likely to improve outcomes. Consensus on proper use of cardiac imaging studies has been hindered by absence of clinical studies that objectively compare the independent treatment-related prognostic information of each test obtained using standardized methods. Uniformity of reporting formats also needs to be improved in order to provide a clearer working scheme for clinicians.

Alternative Imaging Modalities in Ischemic Heart Failure (AIMI-HF) (Project I-A of the Imaging Modalities to Assist with Guiding Therapy and the Evaluation of Patients with Heart Failure, IMAGE-HF program) is a multicenter trial with the primary objective of comparing the effect of HF imaging strategies on the composite clinical endpoint of cardiac death, myocardial infarction (MI), resuscitated cardiac arrest and cardiac re-hospitalization (worsening heart failure, acute coronary syndrome, arrhythmia). Patients with an ischemic heart disease (IHD) etiology will follow HF imaging strategy algorithms according to the question(s) asked by the physicians (for example, is there ischemia and/or viability?), in agreement with their local clinical practices for standard and alternative imaging. Patients will be randomized to either standard imaging modalities for ischemia and/or viability (SPECT) or advanced imaging modalities, namely cardiac magnetic resonance imaging (CMR) or positron emission tomography (PET). Secondary objectives include the effect of HF imaging strategies on the incidence of revascularization procedures, left ventricular remodeling, HF symptoms and quality of life, as well as a health economic evaluation. A biomarker substudy (on renal function, left ventricular remodeling and a selected set of biomarkers), assessing mechanisms underlying specific cardiovascular events, is also planned (see Additional file 1).

#### Coronary revascularization and ischemic heart failure

Among patients with coronary artery disease (CAD) and heart failure, mortality rates range from 10 to 60% at 1 year [1-11]. CAD is the most common cause of HF, however the role of revascularization in these patients is often unclear. Significant concerns remain about perioperative morbidity and mortality [8,10-14]. The recent Surgical Treatment for Ischemic Heart Failure (STICH) trial [15] did not demonstrate a significant benefit for coronary artery bypass graphing (CABG) surgery compared to medical therapy, for the primary endpoint of all-cause mortality in patients with LV dysfunction (ejection fraction {“EF”} ≤ 35%) and coronary disease eligible for CABG; although there was benefit for secondary endpoints of cardiovascular death and cardiovascular endpoints. STICH focused on IHD rather than on chronic HF with systolic dysfunction, and the outcomes of the many patients who were screened but did not undergo revascularization remain unknown [16]. Unfortunately, the STICH trial has not provided the final answer on the role of revascularization for patients with chronic HF; nor did it evaluate the role of advanced imaging in decision making for revascularization in this patient population.

#### Imaging in ischemic heart failure

Increasingly over the past three decades, information describing cardiac structure, function, perfusion, hemodynamics, and metabolism obtained from noninvasive cardiac imaging studies has been used to guide management decisions for patients with HF. Although this anatomic and physiologic information adds value to clinical care, an accepted imaging strategy has not evolved that tailors the testing sequence to specific presenting features of individual patients to efficiently identify the treatment strategy most likely to improve outcomes. Consensus on proper use of cardiac imaging studies has been hindered by the absence of clinical studies that objectively compare the independent treatment-related prognostic information of each test obtained using standardized methods.

Observational data has demonstrated that methods to define ischemia, viability and scar can identify high risk patients likely to benefit (or not) from revascularization [17-22].

The long-term impact of newer or alternative imaging strategies used for the revascularization decision processes has not been evaluated prospectively in HF. Revascularization has the potential to restore function to dysfunctional viable myocardium but not scar. Our group and others have shown that patients with dysfunctional but viable hibernating myocardium are at high risk for cardiac events if they do not undergo timely revascularization [20,23].

Until recently, data from predominantly observational studies had shown that when viability is present, patients have better outcomes with revascularization [24-26]. The PET and Recovery Following Revascularization (PARR-2) trial [27] represents the largest randomized study to evaluate viability imaging in patients with severe LV dysfunction. Overall, there was a trend for benefit for Fluorodeoxyglucose (^18^F) positron emission tomgoraphy scan (FDG PET) assisted management over standard care. When the adherence to imaging recommendations was considered, there was a significant outcome benefit. A high risk subgroup demonstrated a significant mortality benefit [20,27]. Recently, in a post-hoc analysis a significant reduction in events was observed in a subset of patients at the Ottawa site (Ottawa-FIVE) [28]. The results suggest outcome benefits can be achieved using FDG PET in an experienced center with ready access to FDG and interactions with HF and revascularization teams.

Although PARR2 was unique as a randomized controlled trial for imaging viability, it was underpowered for the primary outcome. Larger prospective randomized studies are needed, although undertaking such studies can be challenging [16,29,30]. The STICH viability study [29] did not include a comparison to late gadolinium enhanced CMR, other modalities, nor evaluate the role of stress induced ischemia. Finally, although care was taken to standardize imaging acquisition and transfer of data, standardization was not as rigorous as has recently been achieved in the CADRE Ontario provincial registry [31].

Results from the STICH Viability substudy [29] suggest that identification of viable myocardium by single photon emission computed tomography (SPECT) or dobutamine stress echocardiography (DSE) do not add value in patients selected for surgical revascularization. The STICH Viability substudy results may be explained by a patient population that was at lower risk, with patients already acceptable for revascularization, having more single vessel disease, infrequent previous CABG, low incidence of renal dysfunction and predominantly without heart failure. For such patients, it may be argued that viability imaging is not needed. This is in contrast to sicker populations in studies such as PARR2 [20,27], where physicians were uncertain about revascularization decisions and, therefore, needed viability assessment. Viability testing was not randomized in STICH [15,16,29]. The authors acknowledged the potential for selection bias [29]. Furthermore, only 19% of patients in the substudy were considered to have nonviable myocardium, which is far less than in most previous studies [29,32,33]. Analyses combining DSE and SPECT results were performed. Ischemia and hibernation imaging were not reported. More advanced (or alternative) ischemia and viability imaging modalities (that is, using PET and CMR) were not evaluated.

Thus the STICH results need to be interpreted cautiously [16,30], and the limitations along with the other observational and randomized data, justify the need for a prospective randomized trial to evaluate imaging strategies in patients with heart failure.

AIMI-HF is a large randomized controlled trial, comparing ‘advanced imaging technologies’ (PET and CMR) to standard imaging (SPECT). The findings will provide policy makers with data to support (or not) further investment in and dissemination of alternative or advanced technologies.

### Study hypotheses and objectives

#### Primary hypothesis

In patients with HF due to IHD with left ventricular ejection fraction (LVEF) ≤ 45%, a management algorithm that applies alternative imaging strategies (PET or CMR) achieves a better clinical outcome measured as the composite clinical endpoint of cardiac death, MI, resuscitated cardiac arrest and cardiac re-hospitalization (hospitalization due to heart failure, acute coronary syndrome or arrhythmia) than an approach with standard care using SPECT imaging.

Secondary hypotheses

1) Compared to standard care, in patients with HF due to IHD with LVEF ≤45% a management algorithm that applies alternative imaging modalities (PET or CMR) achieves: a) more efficient use of revascularization procedures with similar complication rates than standard care imaging strategies; b) better HF and angina symptom reduction; c) better quality of life (QoL), measured using MLHFQ and EQ5D; and d) is cost-effective.

2) In patients with HF due to IHD with LVEF ≤45%, a HF management algorithm that applies PET achieves a better primary (composite clinical endpoint) and secondary outcomes (revascularizations, remodeling, QoL, cost effectiveness) compared to one that applies CMR.

#### Primary objective

The primary objective of AIMI-HF is to compare the effect of HF imaging strategies on the composite clinical endpoint of cardiac death, MI, resuscitated cardiac arrest and cardiac re-hospitalization (WHF, ACS, and arrhythmia). Patients with HF due to an ischemic heart disease (IHD) etiology of LV dysfunction will follow HF imaging strategy algorithms according to the question(s) asked by the physicians (Is there ischemia and/or viability?), in agreement with their local practices for standard and alternative imaging.

#### Secondary objectives

To compare the effect of *HF imaging strategies* on:

1. The incidence of revascularization procedures (percutaneous coronary intervention {PCI}, CABG).

2. LVEF,

3. HF symptoms and New York Heart Association Functional Class (NYHA) class.

4. QOL (Minnesota Living with Heart Failure questionnaire (MLHFQ), the EQ5D).

5. Health economics. Costs will be estimated through regression analysis and cost effectiveness will be assessed through decision modeling.

6. The safety of imaging tests measured by cumulative radiation, adverse reactions to imaging contrast agents and stress testing agents will also be determined.

## Methods/Design

The AIMI-HF is a randomized controlled trial to compare the effectiveness of HF imaging strategies in patients with HF due to IHD. Patients enrolled will have LV systolic dysfunction due to IHD where evaluation of ischemia and viability is relevant. Patients will be allocated in a concealed fashion to standard (SPECT) versus advanced (PET or CMR) imaging. In addition, a registry will be maintained of patients undergoing standard or advanced imaging based on clinical decisions.

A survey sent to participating centers revealed that most of them could not provide stress echocardiography consistently within the requested timeframe as per the research protocol. This was especially true for dobutamine stress-echo (DSE) and viability protocols. The decision not to include this method was mainly due to statistical considerations; since if only a few centers elected to use this standard method, there may not be enough patients to adequately compare it with other methods (and site bias might also be involved).

### Study participants

Patients with clinical HF (see Table 1 for definition) or severe LV systolic dysfunction who need further definition of ischemia, viability or scar and meet the following inclusion and exclusion criteria, will be considered for entry into this trial. Patients will be prospectively randomized to standard (SPECT) versus advanced (PET or CMR) imaging. Patients who meet inclusion criteria but cannot be randomized due to clinical management decisions, yet undergo standard or advanced imaging, will be entered into a registry.

**Table 1 T1:** Criteria for the clinical diagnosis of heart failure

**At least one of each of the following symptoms and signs in the last 12 months:**^**a**^	
**Symptoms**	**Signs**
▪ Paroxysmal nocturnal dyspnea	▪ Pulmonary rales (post cough)
▪ Orthopnea	▪ Jugular venous pressure (JVP) ≥5 cm above sternal angle
▪ Dyspnea upon mild or moderate exertion	▪ Lower extremity oedema
	▪ Chest x-ray demonstrating pleural effusion, pulmonary congestion, or cardiomegaly

^a^If LVEF is 30% or less, no signs or symptoms of HF are required for eligibility.

Inclusion criteria:

• Age >18 years

and

• Known or highly suspected coronary artery disease (CAD) documented by coronary angiography or by history of previous MI or evidence of moderate ischemia or scar based on prior imaging.

and

• LV dysfunction most likely attributable to ischemic heart disease with EF ≤45% measured by any acceptable means (echo, nuclear RNA, PET or SPECT perfusion, angiography, CMR) within the previous 6 months and NYHA class II to IV symptoms within the past 12 months or

• LV dysfunction most likely attributable to ischemic heart disease with EF ≤30% measured by any acceptable means (echo, nuclear RNA, PET or SPECT perfusion, angiography, CMR) within the previous 6 months AND NYHA class I within the past 12 months.

Exclusion criteria:

• Severe medical conditions that significantly affect the patient's recommended management (for example, severe COPD, active metastatic malignancy) and would preclude revascularization.

• <4 weeks post-ST segment elevation myocardial infarction (STEMI)

• Already identified as not suitable for revascularization

• Emergency revascularization indicated

• Severe valvular heart disease requiring valve surgery

• Pregnancy, breast feeding

• Potential for non-compliance to tests involved in this protocol

• Incapacity to provide informed consent

### Randomization

Patients will be randomized according to a pre-defined randomization scheme and availability of imaging procedures at individual participating centers. All eligible patients will be randomized to either standard or advanced imaging modalities for ischemia and/or viability testing. Participating sites with the capability for two advanced imaging modalities will then be further randomized between each modality. If randomization is not possible due to local site factors, the patient can be entered into the registry (Figure 1). The ratio of advanced to standard imaging will be 2:1.

**Figure 1 F1:**
[figure not shown]
Overall randomization scheme for patients enrolled in Alternative Imaging Modalities in Ischemic Heart Failure (AIMI-HF).

### Blinding

The study is not blinded given the nature and purpose of the interventions. Knowledge of imaging results and potential gained from the intervention will need to be considered to implement the appropriate treatment strategy. Therefore, performance bias (that is, systematic differences between groups in the care provided or exposure to factors other than the interventions of interest) and attrition bias (that is, systematic differences between groups in withdrawals from the study) may occur. Detection bias is still a potential concern, but an independent assessor will evaluate the objectively defined primary outcome and an adjudication committee will independently review and adjudicate each clinical event blinded to treatment randomization.

### Measurements

Standard imaging protocols have been defined by the IMAGE-HF Standardization team, using nationally recognized protocols (Additional file 2) GFR will be estimated (eGFR) using the Modified Diet in Renal Disease (MDRD) equations based on current recommendations [34-37]. CBC, electrolytes, urea, creatinine will be measured locally on randomization. This creatinine measurement will serve for local eGFR assessment (to ensure CMR eligibility). Further laboratory analyses will be collected and stored for future biomarkers analyses (at baseline and at 1 year in a subgroup of patients; Additional file 1).

### Subject evaluation

At baseline, demographic and clinical data will be collected from all participants on standardized case report forms. These data will be collected from the most recent, routine history and physical examination that has been completed by the treating physician. Quality of life questionnaires (EuroQol and Minnesota Living with Heart Failure) will be administered. In addition, the above-mentioned laboratory samples will be collected. To address a secondary objective, whenever possible, an echocardiogram will be performed if LV ejection fraction has not been determined by echocardiography within 6 months prior to randomization. As much as possible, imaging procedures will be performed within 4 weeks after entry into the trial. Subsequent telephone follow-up and repeat blood work will be performed on a predetermined schedule (Table 2). If the patient cannot be reached by telephone for their final assessment, a query will be made at government or national health care resources to verify if any corresponding events have occurred since the last visit (search of corresponding codes for cardiac death, MI, cardiac arrest and cardiac re-hospitalization for WHF, ACS, or arrhythmia). A follow-up echocardiogram will be requested at one year (LV remodeling, LVEF). Within 3 months of the baseline scan the treating physician will be asked to record the HF management plan.

**Table 2 T2:** Patient assessment schedule

	**Baseline**	**3 months**	**6 months**	**12 months**	**18 months**	**24 months**	**36 months**	**48 months**
Imaging (SPECT, PET or CMR)	x							
Blood work	x			x				
Demographic and history	x							
Clinical data collected	x			x				
EuroQol questionnaire	x	x	x	x	x	x	x	x
MLWHF questionnaire	x	x	x	x	x	x	x	x
Telephone follow-up		x	x	x	x	x	x	x

*CMR* cardiac magnetic resonance, *MLWHF* Minnesota Living with Heart Failure, *PET* positron emission tomography, *SPECT* single photon emission computed tomography.

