For the secondary hypothesis, using the Cox regression model for comparing the advanced modalities PET versus CMR with an approximate 1:1 patient allocation, a sample size of 548 patients per modality is needed considering an anticipated rate for the composite clinical endpoint of 30% after 1 year, a level of significance of 0.05, a power of 80% and a loss to follow-up of 10%. The sample size calculation is complicated by the fact that 766 patients (383 per group) from the registry (in which patients in the registries were clinically directed to PET or CMR) will be combined in the analysis with the 330 patients (165 per group) from the randomized part of the study (in which patients in the randomized study will be randomly allocated to PET versus CMR versus standard modality) for a total of 1096 patients (548 per group). For a sample of 1096 patients, a Cox regression of the log hazard ratio of the composite clinical endpoint on the group allocation variable (PET versus CMR) with a conservative standard deviation of 0.5 (based on an approximate equal allocation to PET and CMR), achieves 80% power at a 0.05 significance level to detect a 40% increase in the hazard ratio to1.4. This increase in the hazard ratio was deemed to be the minimal clinically important difference based on a consensus among the IMAGE-HF investigators. The sample size includes an adjustment to accommodate confounding by indication for allocation patients to PET versus CMR by incorporating a multiple regression of the group allocation variable on the other covariates in the Cox regression model; a conservative estimate of this confounding was considered by taking a value of 0.25 for the multiple correlation coefficient R for the relationship between the group allocation variable and the set of covariates identified.

The total sample size is thus 1,096 + 165 = 1,261.

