#### Secondary analysis (PET versus CMR)

For the secondary analysis, comparing the PET and CMR modalities, potential confounding variables of the relationship between the imaging technologies and the primary endpoint will be assessed. In particular, propensity scores based on patient factors (for example, in/outpatient, NYHA class, HF duration, diabetes, atrial fibrillation) and site factors (for example, time-to-imaging, time-to-therapy) will be used in the analysis if necessary to adjust for potential differences between PET and CMR. A Cox proportional hazard models will be used to assess the occurrence of the endpoints between the imaging technologies (the model will include a group indicator variable) adjusting for any pertinent baseline differences identified. The proportional hazards assumption underlying the Cox model will be assessed. The secondary outcomes will be analyzed in a similar fashion.

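### Baseline NYHA class may be up to about 12 months old, which could leave residual confounding in the mostly non-randomised PET versus CMR comparison

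*Protocol article*

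**What the plan says.** All references are to the Protocol article.

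- **Subject evaluation.** Of baseline demographic and clinical data: "These data will be collected from the most recent, routine history and physical examination that has been completed by the treating physician". No maximum age is given for that examination. The quality-of-life questionnaires are administered at baseline. For LVEF, where possible, "an echocardiogram will be performed if LV ejection fraction has not been determined by echocardiography within 6 months prior to randomization".
- **Measurements.** "CBC, electrolytes, urea, creatinine will be measured locally on randomization".
- **Study participants.** One entry route needs "NYHA class II to IV symptoms within the past 12 months". The route for EF of 30% or less with NYHA class I has the same window. Table 1 asks for "At least one of each of the following symptoms and signs in the last 12 months", waived if LVEF is 30% or less.
- **Registry.** Registry patients must be eligible, and the same evaluation applies to them.
- **Sample size.** PET versus CMR combines 330 randomised with 766 registry patients; "patients in the registries were clinically directed to PET or CMR".
- **Secondary analysis (PET versus CMR).** Adjustment, if needed, uses "propensity scores based on patient factors (for example, in/outpatient, NYHA class, HF duration, diabetes, atrial fibrillation"), together with site factors. The primary analysis gives the same examples.
- **Secondary outcomes.** NYHA class and HF symptoms are compared by chi-square test, with logistic regression if baseline differences call for it.

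**The concern.** The other baseline measures are tied to study entry: laboratory tests at randomisation, questionnaires at baseline, LVEF within 6 months. NYHA class and symptoms are tied only to the last routine examination, although class can change with treatment or decompensation. In/outpatient status, another named covariate, can also change after an older examination.

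This matters most for PET versus CMR. About 70% of those patients are not randomised, so the comparison depends on covariate adjustment. A misclassified confounder is only partly adjusted for, and the remainder does not shrink as the sample grows. The R = 0.25 allowance in Sample size does not help: it enlarges the sample to cover lost precision and removes no bias.

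**Working it through.** **1. How old can the recorded class be?** Subject evaluation sets no limit. Study participants requires the qualifying NYHA class within 12 months, and the most recent examination cannot predate the one that documents that class. The practical bound is therefore about 12 months, twice the 6-month LVEF window.

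**2. The plan's own figure.** Events = (1.960 + 0.842)² / [0.5² × (ln 1.4)²] = 277.3. Dividing by 1 − 0.25² = 0.9375 gives 295.8. Dividing by the 30% event rate gives 986.0, and by 0.90 for losses gives 1,095.6, so 1,096. This reproduces, and 1,096 + 165 = 1,261. The registry share is 766/1,096 = 0.699. The sample size is not in question.

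**3. Bias if current class drives the choice.** The following inputs are assumptions, because the article gives none of them:
- true PET/CMR hazard ratio of 1;
- current class III-IV in 35% of one registry group and 45% or 55% of the other;
- event-rate ratio θ for class III-IV of 1.5 or 2.0;
- a share m = 10%, 20% or 30% of recorded classes wrong, equally in both groups.

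For group g with share p in class III-IV, and recorded level w:
- n(g,w) = p·P(w | III-IV) + (1 − p)·P(w | I-II)
- π(g,w) = p·P(w | III-IV) / n(g,w)
- relative rate r(g,w) = 1 + (θ − 1)·π(g,w)
- adjusted ratio = ΣW·r(1,w) / ΣW·r(2,w), with W = n(1,w)·n(2,w) / [n(1,w) + n(2,w)]

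Worked case: 55% against 35%, θ = 2, m = 20%.
- Recorded I-II: n = 0.47 and 0.59; π = 0.234 and 0.119; r = 1.234 and 1.119; W = 0.262.
- Recorded III-IV: n = 0.53 and 0.41; π = 0.830 and 0.683; r = 1.830 and 1.683; W = 0.231.
- Adjusted registry ratio = 0.746/0.682 = 1.094. The crude ratio is 1.55/1.35 = 1.148, so ln 1.094 / ln 1.148 = 65% of the NYHA confounding remains.
- Pooled with the randomised 30%: exp(0.699 × ln 1.094) = 1.065.
- Type I error: δ = √(296 × 0.25 × 0.9375) × ln 1.065 = 8.33 × 0.063 = 0.52; Φ(−1.96 − δ) + 1 − Φ(1.96 − δ) = 0.082.

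Over all combinations:

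| Misclassified | Confounding left | Registry HR | Pooled HR | Type I error |
|---|---|---|---|---|
| 0% | none | 1.00 | 1.00 | 0.050 |
| 10% | 37% | 1.02-1.05 | 1.01-1.04 | 0.051-0.060 |
| 20% | 65% | 1.03-1.09 | 1.02-1.07 | 0.053-0.082 |
| 30% | 85% | 1.04-1.12 | 1.02-1.09 | 0.055-0.105 |

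Which modality has the sicker patients is unknown. If the groups are swapped, the ratios fall below 1.

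**4. Are the assumed imbalances within the plan's own allowance?** For two equal groups, the correlation of class with modality is d / [2√(p̄(1 − p̄))], where d is the difference in shares and p̄ their mean. For 55% against 35% it is 0.20/0.995 = 0.20 in the registry, about 0.699 × 0.20 = 0.14 pooled, and its square 0.020 is about a third of the R² of 0.0625. The assumed range fits inside R = 0.25.

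**5. If the recorded class drives the choice.** Within a recorded level, current class is then unrelated to modality. So π(1,w) = π(2,w), the relative rates are equal, and the adjusted ratio is exactly 1 for any m. Simulation shows the same contrast (383 per group directed, 60% against 40%, hazard ratio for class 1.8 or 2.5, 20% or 30% discordant). The PET/CMR hazard ratio is about 1.06 to 1.13 when current class drives the choice, and 0.98 to 1.01 when recorded class does. Those inputs are stronger than in step 3 and serve only to show that the mechanism decides the result.

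**The case against.** - **Mechanism.** The record comes from the treating physician's own latest examination, which may be what guided the choice of scan. In that case no NYHA confounding remains after adjustment, however old the class. This stands, and it makes the bias conditional.
- **Current status is partly captured.** MLHFQ and EQ5D are administered at baseline to registry patients too, and the covariate list is only by way of example. This stands in part. Adding a questionnaire-like score to the simulation (assumed separation between classes of 1 to 1.5 SD) generally reduced the bias, to about 1.05 to 1.09, but did not remove it. The plan does not name these scores as covariates.
- **No time limit at all.** A reader of Subject evaluation alone might infer this. The eligibility window bounds the class at about 12 months.
- **Much larger error inflation.** A reader might reach it by assuming 65% against 35% in the registry. That is a correlation of 0.30 there and 0.699 × 0.30 = 0.21 pooled. Its square, 0.044, would use about 70% of the R² of 0.0625 that the plan calls conservative for the whole covariate set. It should carry no weight.
- **Bias in the randomised comparison.** A reader might infer this because NYHA class and symptoms are also outcomes. The data source is the same in both arms, and the chi-square test uses no baseline. At most, an optional baseline adjustment, or an analysis of change, loses precision.
- **Full protocol or case report form.** Either may set a window or record the examination date, and that NYHA class belongs to the clinical data is inferred. Both are fair. The point rests on the source rule that the article does state.

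**Conclusion.** The point holds in a limited form. The stated source allows NYHA class and symptoms up to about 12 months old as baseline, in a comparison that is 70% non-randomised and names NYHA class as a propensity factor. Residual confounding follows only if modality was chosen on a status other than the recorded one; the article does not settle this.

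Where it does follow, the assumed inputs put the pooled hazard ratio at about 1.01 to 1.09 under the null. That is small against the target of 1.4, although type I error reaches about 10% at the top of the range. These figures are a sensitivity range, not an estimate. They treat NYHA class as the only confounder, in two levels, with the same misclassification in both groups. The documents do not support saying that PET versus CMR is left confounded. The change is worth making because it is cheap and protects the comparison that randomisation mostly does not cover.

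**What to change.** In Subject evaluation, record NYHA class, HF symptoms and in/outpatient status, with the date, at the enrolment contact where EQ5D and MLHFQ are already administered. Do this for randomised and registry patients alike, before the index scan result is known. Use these values in the PET versus CMR propensity model, and consider adding the baseline MLHFQ and EQ5D scores. The routine examination can remain the source for history and demographics.

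The enrolment value works under either mechanism in the working, provided an older class affects outcome only through the current one.

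For patients already enrolled, record the examination date and run a sensitivity analysis limited to recent values.

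The cost is a few extra case report form fields, with no added visit and no change in sample size. The 249 patients enrolled when the article was written keep the old source; the remaining 1,261 − 249 = 1,012, about 80%, would benefit.
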